### Randomisation

If safety is met, the remaining participants will be randomised to all doses or placebo on a 1:1:1:1 basis, stratified by centre and donor type. Participants observed in the safety run will not be included in the analysis.

### Analysis

Analysis will occur at the end of the trial comparing differences in DGF proportions between each dose and the control along with CIs. Safety assessments during the randomisation stage will include routine renal function and urine tests, with further investigation (eg, renal ultrasound and Doppler) as appropriate and complement activity and Mirococept levels as per the current protocol.

In the event that DGF rate and safety outcomes are similar in more than one dosing group, the final decision on which dose to take forward to the pivotal Phase III clinical trial will include the secondary outcome measures. Of these, the most important are: functional DGF rate (where the fall in creatinine is less than 10% per day for three consecutive days); and AUC based on the drop in serum creatinine level in the first 2 weeks after transplantation where the patient does not require postoperative dialysis. If the combined primary and secondary endpoints of efficacy and the safety outcomes do not discriminate between two doses, then the lower of the two doses would be taken forward to the next trial.

This would be a confirmatory Phase III trial (to be separately funded) with two arms—the best-selected dose from the current trial vs the placebo control—each of which requiring 124 patients. Differences in DGF rates would be compared between the treatment and control arms using logistic regression adjusting for stratification factors.

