## Randomisation procedure/code break

### Randomisation

Recruiting site personnel will be responsible for randomisation of individual participants in the multi-arm randomised stage.

If safety is met, the remaining participants will be randomised to all doses meeting the safety criteria or placebo on a 1:1:1:1 basis, stratified by centre and donor type (there are two main types of deceased donation—DBD and DCD).

The randomisation service will be provided by King’s College London (KCL) Clinical Trials Unit (CTU).

Once ensuring all inclusion and exclusion criteria (with the exception in some cases of crossmatch results) are met and written informed consent is obtained, the participant must be registered on the MACRO trial database. Following registration of the participant on MACRO, a participant ID will be generated. The participant can then be randomised, using their participant ID, via KCL CTU’s randomisation service made accessible to all the centres via the internet (https://cturandomisation.iop.kcl.ac.uk/index).

A step-by-step guide to registering and randomising a participant will be provided to centres in their site files.

In the event of a drug kit number being assigned, and the transplant not going ahead, the pack must be quarantined in the area pre-designated for quarantined kits, until it can be reassigned for use. The coordinating centre should be informed as a matter of urgency if this situation arises so the unused drug kit can be reassigned for future use.

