### Sample size

Nine patients will be needed for the safety run. Allowing for a 10% drop-out rate, the target sample size will be 10 patients for this stage.

For the main multi-arm randomised placebo-controlled stage, the required sample size was calculated using a selection theory approach as proposed by Simon *et al*.^26^ Software from the Centre for Clinical Research and Biostatistics, Hong Kong was used: (https://www2.ccrb.cuhk.edu.hk/stat/phase2/Randomized.htm).

The parameters for this calculation are p=0.30, D=0.20 and k=4, where p is the estimated percentage of the lowest response rate among all treatments, D is the difference in response rate between the best dose of Mirococept and all the other treatment groups including placebo, and k is the number of treatment arms.

A sample size of 144 (36 in each arm) will be required to correctly identify the best dose of Mirococept with 90% probability. 30 patients per arm will be required if two of the proposed doses are well-tolerated and 20 patients per arm if only one dose is well-tolerated in the safety run. Allowing for a 10% drop-out rate, the target sample size for a 4-arm study will be 160 participants (40 in each arm).

Overall, up to 170 participants are needed for the safety component and main randomised study.

A sample size of 40 per arm will produce a two-sided 95% CI for the difference in population proportions with a precision that is equal to ±21.1% when the estimated DGF rate in the treatment arm is 30% (vs 50% in placebo).

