### Effect size

Reduction in DGF from 50% to 30% (ie, a 20-point reduction; 40% relative reduction), control versus treatment, is predicted. The base rate of 50% is modelled on Guy’s Hospital audit data over the past 3 years and consistent with DGF rates of 60% and 40% reported for DCD and DBD, respectively, in a Cambridge study of 525 consecutive kidney transplants.^27^ The estimated 20%-point reduction is justified by a life-sustaining rat isograft model in which the frequency of non-functioning grafts was reduced from 73.3% in the control arm to 36.4% in the treatment arm.^20^ Rat donor kidneys with IGF had more rapid recovery than controls, with a relative reduction in AUC of creatinine during week 1,^20^ justifying use of this measure as a secondary endpoint in the trial. A clinical trial of ex vivo normothermic perfusion in DCD kidneys was powered for a 15%-point reduction in DGF (from 50% to 35%; a 30% relative change) with power of 80% and statistical significance of α=0.05, that is, within range of the predicted effect size.^28^

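### Randomisation is stratified by centre and donor type, but the stated dose-versus-placebo analysis names no adjustment for either; the gain from adding it is small and nearly free

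*Protocol article*

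**What the plan says.** - **Randomisation.** The Randomisation section under Statistics has participants "randomised to all doses or placebo on a 1:1:1:1 basis, stratified by centre and donor type". The section on the multi-arm trial and the Randomisation procedure section name the same two factors. No section gives the reason for choosing them.
- **This trial's analysis.** The Analysis section describes "comparing differences in DGF proportions between each dose and the control along with CIs". It calls these differences neither crude nor adjusted, and it names no stratified method.
- **The next trial's analysis.** The same section says that DGF rates in the separately funded Phase III would be compared "using logistic regression adjusting for stratification factors". The multi-arm trial section says that randomisation will be the same in that second stage.
- **Prognostic strength.** The Effect size section calls the 50% base rate "consistent with DGF rates of 60% and 40% reported for DCD and DBD" in a cohort of 525 transplants.
- **Size and precision.** The Sample size section rests on selection: "A sample size of 144 (36 in each arm) will be required to correctly identify the best dose of Mirococept with 90% probability". It adds a two-sided 95% interval at 40 per arm "with a precision that is equal to ±21.1% when the estimated DGF rate in the treatment arm is 30% (vs 50% in placebo").

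**The concern.** Stratified randomisation balances the arms on a factor that predicts the outcome. An analysis that ignores the strata leaves the between-stratum variation in the standard error, and it cannot correct imbalance among the patients finally analysed. Here the cited gap between DCD and DBD is 20 points, as large as the treatment effect the trial is sized around. The article pairs the same randomisation with an adjusted analysis in Phase III and with none named in Phase IIa, without explanation.

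Some imbalance can remain despite stratification. A participant may be randomised before cross-match results are known (Table 2), a transplant may not go ahead after a kit is assigned (Randomisation), withdrawn participants are replaced (Withdrawal of participants), and centre crossed with donor type over four arms leaves small cells. At stake are some precision in a trial with 36 evaluable patients per arm, and protection of the effect estimate that, under the Secondary objectives, is meant to power Phase III.

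**Working it through.** **Inputs.** From Sample size and Effect size: DGF 50% on placebo and 30% on the best dose; 36 evaluable and 40 recruited per arm; DCD 60%, DBD 40%. Assumptions: a 50:50 donor mix (the mix at which 60% and 40% average to 50%) and the same 20-point effect in both donor types, so treated rates are 40% and 20%.

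**1. Reproduce the stated precision.** The unstratified variance sum is 0.5×0.5 + 0.3×0.7 = 0.46.
- 40 per arm: 1.96×√(0.46/40) = 0.210, or 21.0 points (stated 21.1).
- 36 per arm: 1.96×√(0.46/36) = 0.222, or 22.2 points.

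The stated figure is therefore, to within 0.1 point, an unstratified calculation.

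**2. Stratify by donor type.** The within-stratum variance is (0.24 + 0.24)/2 = 0.24 for placebo and (0.24 + 0.16)/2 = 0.20 for the treated arm, sum 0.44.
- 40 per arm: 1.96×√(0.44/40) = 0.206, or 20.6 points.
- 36 per arm: 1.96×√(0.44/36) = 0.217, or 21.7 points.
- Ratio: √(0.44/0.46) = 0.978, a gain of 2.2%. In patients, 36×0.46/0.44 = 37.6, so fewer than 2 extra per arm.

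With a DCD share of 30% to 50% and a constant risk difference, risk ratio or odds ratio, the gain runs from 1.3% to 2.2%.

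**3. Centre.** The document gives no centre effect. If centre-level DGF risk had an SD of 5, 10 or 15 points (assumed), the combined gain at 40 per arm would be 2.8%, 4.4% or 7.3%, before any cost of adjusting for many small centres.

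**4. Residual imbalance.** A 10-point difference in DCD share (3.6 patients of 36) shifts the crude difference by 0.10×20 = 2 points. The standard error is √(0.44/36) = 11.1 points, so the shift is about 0.18 SE. It is also less than one patient's outcome (1/36 = 2.8 points).

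**5. Coverage, by simulation.** 36 per arm, balanced donor split, rates as above, nominal 95% Wald intervals. The true SD of the difference is 0.111.

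| Interval | Mean SE | Coverage |
|---|---|---|
| Crude | 0.111 | 94.4–94.5% |
| Stratified, plug-in variance | 0.107 | 93.8% |
| Stratified, n−1 variance in each stratum | 0.107×√(18/17) = 0.110 | about 94.3% |

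The crude plug-in interval averages 21.8 points, already a little short of the 22.2 in step 1. Against it, the n−1 stratified interval (1.96×0.110 = 21.6) saves only about 0.2 point. The 2% gain is a like-for-like figure.

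**6. Dose selection.** The exact binomial calculation with ties broken at random returns the stated 36, 30 and 20 per arm for 90% correct selection. If DCD counts vary at random by up to 2 per arm of 36, the probability of selecting the best dose is 90.7% on crude rates and 90.9% on adjusted rates.

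**The case against.** **The document never says crude.** This is correct. A Mantel-Haenszel or standardised risk difference is also a difference in proportions with a CI. The choice of covariates and the pooling of centres are commonly left to the SAP, which is not shown, and the article condenses a fuller protocol. A reader might infer that the team has committed to an unadjusted analysis; the text does not establish that. What remains is that the section does address adjustment and assigns it only to Phase III, and that the precision figure is an unstratified one.

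**The crude interval is not materially too wide.** This also stands. At the cited rates its SE is close to the true SD and its coverage is slightly below 95%. A reader might infer intervals about 9% too wide. That needs strata at 70% and 30% (true SD √(0.38/36) = 0.103 against a reported 0.112), which the document does not give. The under-coverage of the simple stratified interval is a fair warning, but it largely disappears with an n−1 stratum variance.

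**The crude Phase IIa estimate is not a different quantity from a standardised one.** Under randomisation both target the same marginal risk difference, so adjustment changes precision and not the estimand. The case for aligning the two stages is consistency alone.

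**The ranking of doses is hardly touched.** Agreed: a 2-point shift matters only when doses are nearly tied, and the 10-point imbalance behind it is an assumption.

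**Conclusion.** The point holds as a modest improvement. The article stratifies by two factors, cites rates showing that one of them is prognostic, and names adjustment only for the next trial. On its own 60% and 40% rates, adjusting for donor type is worth about 2% of the interval half-width (22.2 to 21.7 points at 36 per arm; 1.3% to 2.2% over the mixes and effect scales tried). It also protects against residual donor-type imbalance at 2 points per 10-point difference in DCD share. These sizes rest on the assumed donor mix and effect scale; any larger gain rests on stratum or centre differences not in the document.

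Nothing here shows the sample size, the selection probability or a future dose decision to be wrong. Nor does the document say that the 20-point donor gap was the reason for stratifying: the 60% and 40% figures are cited there to support the base rate.

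**What to change.** State in the Analysis section that each dose-versus-placebo risk difference is adjusted for donor type, by Mantel-Haenszel weighting or by standardisation from a logistic model, with a small-sample (n−1) stratum variance where the stratified form is used. Add centre where cells allow, with small centres pooled by a rule fixed before unblinding. Report the crude difference as supportive. If the full protocol or SAP already specifies this, bring the Analysis section into line with it.

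The cost is a few sentences of wording. Both factors are already recorded for randomisation, and the sample size does not change.

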### Effect size

Reduction in DGF from 50% to 30% (ie, a 20-point reduction; 40% relative reduction), control versus treatment, is predicted. The base rate of 50% is modelled on Guy’s Hospital audit data over the past 3 years and consistent with DGF rates of 60% and 40% reported for DCD and DBD, respectively, in a Cambridge study of 525 consecutive kidney transplants.^27^ The estimated 20%-point reduction is justified by a life-sustaining rat isograft model in which the frequency of non-functioning grafts was reduced from 73.3% in the control arm to 36.4% in the treatment arm.^20^ Rat donor kidneys with IGF had more rapid recovery than controls, with a relative reduction in AUC of creatinine during week 1,^20^ justifying use of this measure as a secondary endpoint in the trial. A clinical trial of ex vivo normothermic perfusion in DCD kidneys was powered for a 15%-point reduction in DGF (from 50% to 35%; a 30% relative change) with power of 80% and statistical significance of α=0.05, that is, within range of the predicted effect size.^28^

## Trial Management Group

The Trial Management Group (TMG) will include the CI, statisticians, clinical trial manager, chief scientific investigator, Senior Post Doctoral Research Associate, clinical research associate and trial staff. The TMG will be responsible for overseeing the trial and will be responsible for the day-to-day management of trial activities.

The TMG will meet regularly to discuss any trial-related activities or issues and will send updates to PIs and their teams. The TMG will review recruitment figures, SAEs and substantial amendments to the protocol prior to submission to the REC and/or MHRA. All PIs and sites will be kept informed of amendments or any trial-related developments.

## Trial Steering Committee

The TSC will provide advice for the conduct of the trial. It will comprise an independent chair and other members—both independent and non-independent. Details of the TSC, frequency of meetings, its members and terms of reference will be described in the TSC charter. The TSC provides overall supervision of the trial and ensures that it is being conducted in accordance with the principles of GCP and the relevant regulations.

The TSC members will meet to discuss trial status, recruitment progress and any other relevant issues and provide recommendations to the TMG/Sponsor.

The TSC will comprise both independent and non-independent members. The TSC Chair will be independent.

## Data Monitoring Committee

A DMC will be constituted prior to the study opening. The role of the DMC is to provide independent advice on data and safety aspects of the trial. The DMC charter will detail membership and terms of reference. The DMC members will be independent and supported by the trial statistician. In order to ensure patient safety throughout the conduct of the trial, the DMC will review and evaluate accumulated safety data, study conduct and progress. The DMC will make the decisions about the continuation, modification or termination of the study.

The DMC members will convene at defined time points stated in the DMC charter.

In addition, during the safety run, a DMC meeting will be convened after each dosing cohort to review safety data and before dose escalation to the next dose is permitted.

A DMC meeting would also be triggered if any of the safety events below occur:

More than one of three occurrences of non-perfusion (day 0/day 1) in each dosing group, or two occurrences in a row between groups, during the safety run, in the absence of technical failure or hyperacute rejection.Two or more patients per dosing group with DGF lasting more than 2 weeks during the safety run.Death of a participant.Or at any other time deemed necessary by the DMC chair.

## Direct access to source data and documents

The Investigators will permit trial-related monitoring, audits, REC review and regulatory inspections by providing the Sponsors, Regulators and REC direct access to source data and other documents (eg, participants’ source data worksheets, blood test reports, radiology reports, histology reports).

## Quality assurance

Monitoring of this trial will be to ensure compliance with GCP and scientific integrity will be managed and oversight retained by the KHP-CTO Quality Team.

Regular data cleans of the eCRF will be carried out by the CI team as per a Data Discrepancy Management Plan to identify any discrepancies not picked up by the eCRF validation system.

## Data handling

The CI will act as custodian for the trial data (figure 2). The following guidelines will be strictly adhered to:

Participant data will be pseudo-anonymised.All pseudo-anonymised data will be stored on a password-protected computer.All trial data will be stored in line with the Medicines for Human Use (Clinical Trials) Amended Regulations 2006 and the Data Protection Act and archived in line with the Medicines for Human Use (Clinical Trials) Amended Regulations 2006 as defined in the KHP-CTO archiving SOP.

**Figure 2 F2:**
[figure not shown]
Data flow. eCRF, electronic case report form; GSTT, Guys and St Thomas’ NHS Foundation Trust.

## Data management

A study-specific data management plan has been created for this trial (online supplemental material). The data collected for this trial is a combination of routine clinical and laboratory test results commonly used in the management of kidney transplant patients and the research samples being collected for the participants at Guy’s Hospital.

### Data collection

The delegated site staff will collect data at each visit as per the schedule of events in online supplemental table 1. Source data will be collected on source data worksheets and through other source documentation. The delegated site staff responsible for data entry will be trained in the use of the eCRF system. Data entered in the eCRF system must be consistent with source data.

Sites must retain all participant records and source data for the duration of the trial for source data verification purposes during monitoring visits. All original signed informed consent forms should be filed in the Investigator Site File.

All applicable fields in an eCRF page should be completed and if data are not available, this should be clearly indicated on the form. The eCRF platform automatically creates a protected audit trail for all data entries and changes. Amendments to eCRF data will be recorded in the audit trail with a time and date stamp, along with a user-specified reason for the implemented change.

The PI may delegate data entry into the eCRF but is ultimately responsible for submitting a complete set of eCRFs for each enrolled participant.

Any supportive paper documentation (including details of any SAE) transmitted from the investigators to the Sponsor should be clearly marked with the trial name and participant trial identifier and age. Any personal information, including the name of the participant, should be removed or rendered illegible to preserve individual confidentiality.

### eCRF database

A web-based eCRF system will be designed using the MACRO system created in collaboration with the trial analyst/s and the CI team and maintained by the KCL CTU for the duration of the project. It will be hosted on a dedicated secure server within KCL.

Access to the trial eCRF platform will be password protected and electronic login credentials will be issued only to authorised individuals. It is a legal requirement that passwords to the eCRF are not shared, and that only those authorised and delegated to access the system are allowed to do so. If new staff members join the study, a personalised username and password should be requested via the Trial Manager, and a request for access to be revoked must be requested when staff members leave the project. Study site staff experiencing issues with system access or functionality should contact the CI or delegate (Trial Manager) in the first instance.

At the end of the study, once all the data reported on the database has been monitored and cleaned, the eCRF will be locked.

## Publication policy

The results of the study will be reported and disseminated at international conferences and in peer-reviewed scientific journals. Once published, a lay summary of the results will be made available to participants who request this information.

## Insurance/indemnity

This study is co-sponsored by KCL and Guys and St Thomas’ NHS Foundation Trust (GSTT). The co-sponsors will, at all times, maintain adequate insurance for the design, management and conduct of the study: (1) KCL through its own professional indemnity (Clinical Trials) and no-fault compensation policy; and (2) GSTT through NHS Resolution cover, in respect of any claims arising as a result of negligence by its employees, brought by or on behalf of a study participant.

## Discussion

DGF affects up to 50% of kidney transplants and is associated with higher rates of acute rejection, reduced graft and patient survival and prolonged hospitalisation. The incidence of DGF has significantly increased over the last two decades, probably due to the increased proportion of DCD and ECD kidneys that are being transplanted. There is an unmet need to treat DGF to improve short- and long-term graft outcomes. Local manipulation of the complement system at the site of its activation has emerged as an attractive and promising target. The lack of efficacy of previous studies with systemically administered agents might be explained by their inability to inhibit complement activation in the renal tubule. The ‘painting’ of the donor kidney before transplantation with Mirococept, a cytotopic analogue of CR1, has the potential to deliver sufficient complement inhibition with minimal systemic side effects.

Following the EMPIRIKAL trial, to our knowledge, this is the second clinical trial to implement this innovative method of ex vivo administration of a cytotopic complement inhibitor (Mirococept) in renal transplantation.

